## Abstract

**Background:**

Diabetes model projects in different regions of Germany including interventions such as quality circles, patient education and documentation of medical findings have shown improvements of HbA1c levels, blood pressure and occurrence of hypoglycaemia in before-after studies (without control group). In 2002 the German Ministry of Health defined legal regulations for the introduction of nationwide disease management programs (DMP) to improve the quality of care in chronically ill patients. In April 2003 the first DMP for patients with type 2 diabetes was accredited. The evaluation of the DMP is essential and has been made obligatory in Germany by the Fifth Book of Social Code. The aim of the study is to assess the effectiveness of DMP by example of type 2 diabetes in the primary care setting of two German federal states (Rheinland-Pfalz and Sachsen-Anhalt).

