## Background

Diabetes is a major and growing health care problem. The number of diabetes patients is expected to increase globally from 135 to 300 million between 1995 and 2025 [1], the vast majority will have type 2 diabetes [2]. The quality of care for diabetic patients in Germany was like in many western countries criticized for more than two decades. The Expert Committee of the Government therefore recommended in 2003 diabetes as a priority area [3]. Epidemiological data from primary care was mostly lacking, although recently published data showed that performance of practices and diabetes control in patients could be better than suggested [4-6]. Quality of care is expected to improve within disease management programs (DMP) by the implementation of evidence-based clinical practice, by means of guidelines, quality circles, educational meetings, outreach visits, patient education and by improving coordination among different health care providers [7,8]. Consequently, clinical guidelines and DMPs for primary care have been developed to improve quality and cost-effectiveness of health care for chronic conditions such as diabetes.

In the reform law of 2002 the German Ministry of Health defined a complicated process for the introduction of DMPs and on 27 February 2003 the Federal Insurance Office accredited the first DMP for type 2 diabetes [9]. Several patient- and provider-oriented interventions within the German-style DMP aiming at decreasing mortality and morbidity of patients with type 2 diabetes reducing micro- and macrovascular complications and increasing quality of life of diabetes patients. The underlying criteria therefore have been developed by the newly formed Coordinating Committee and have gone through a tough process of certification before they have been regulated by law by the Ministry of Health in 2002 [10]. The German DMP structure is tightly linked to financial incentives for the sickness funds, i.e. it is linked with the risk structure compensation (= RSC) which was introduced to compensate for differences in the risk structure of the insured population. [9]. Besides the requirement of a comprehensive documentation and the obligation to provide guideline-oriented healthcare the statutory health insurances are obliged to evaluate DMPs by the Fifth Book of Social Code [9,11].

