However, until now valid scientific data showing the effectiveness of the German Diabetes-DMP are missing. Recently published data of diabetes model projects in the region of Nordrhein, Sachsen-Anhalt and Baden-Wuerttemberg show improvements of HbA1c levels, blood pressure and occurrence of hypoglycaemia [12-14]. However, the duration of these model projects was too short to draw conclusions concerning clinical endpoints (i.e. a cardiovascular events, amputation rate) and bias because of the preferred inclusion of highly motivated patients can not be excluded [15].

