#### Selection of participants

500 GPs in Rheinland-Pfalz and 500 GPs in Sachsen-Anhalt participating in the Diabetes-DMP will be recruited by an invitation letter giving information about the study project. From those who will accept to participate, 100 GPs will be randomized in the DMP group 1 and 100 in the DMP group 2. All patients with a type 2 diabetes out of these practices insured at the general regional health funds (*Allgemeine Ortskrankenkassen = AOK*) and participating in the DMP will be included in the study then. Incomplete participation in the interventions will be an exclusion criterion in the DMP group 2.

For the control group 4000 AOK patients out of practices not participating in the DMP will be detected through diabetes tracer medication and age (> 50 years) and will be matched. Participation in a DMP offered by another health fund is an exclusion criterion in the control group.

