### Timeframe of the study

The study team will start to invite GPs at the end of September 2005. After receiving a written declaration of their willingness to participate in the study and to accept random assignment to the different groups GPs will be randomized.

Patient inclusion and pre-data collection will start in 2005. The observation period will be 24 months.

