## Discussion

There are specific difficulties in evaluating the effectiveness of complex interventions such as disease management programs [19], particularly, in our case that implementation process has already started [15]. At the moment it is not conceivable to which phase of the implementation process the DMP actually has preceded. However, the DMP group 2 represents an ideal implementation of the DMP within the scope of the German law regulation.

To adapt the evaluation design to the real conditions of diabetes care in Germany at the moment, but also to consider the ongoing implementation process we have chosen the design of a prospective randomized-controlled comparison of the two DMP groups embedded in the quasi-experimental design of a controlled before-after study with a blinded control group. The quasi-experimental design is predetermined because allocation to the control group can not be perfomed randomly and because baseline values for patients participating in the DMP have not been documented.

A fully experimental design with a randomized control group was rejected by the authors, because this could create an artificial care situation. That is informing patients and GPs of the control group about the study and probably asking for completing any questionnaires would introduce an enormous bias.

According to the theoretical model for design and evaluation of complex interventions by Campbell et al the presented study can be assigned to phase III and IV (15, 20). However, pilot projects have shown that an observation period of 24 months will be too short to show significant differences in severe clinical endpoints (i.e. amputations, diabetic renal insufficiency, cardio-vascular events). Therefore it was decided to have a combination of HbA1c and blood pressure as primary endpoint in the randomized part of the trail and prescriptions in the quasi-experimental part of the trial.

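### DMP 1 takes patients still in the programme in 2005, while controls are chosen by other rules with no retention condition, so the comparison with routine care speaks only for patients who remain in the DMP

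*Protocol article*

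**What the plan says.** Under Selection of participants, GPs already in the Diabetes-DMP are invited. After randomisation, their AOK-insured type 2 patients who are "participating in the DMP will be included in the study then". The Background states that "on 27 February 2003 the Federal Insurance Office accredited the first DMP for type 2 diabetes"; the abstract has "In April 2003 the first DMP for patients with type 2 diabetes was accredited". Under Timeframe of the study, GPs are invited from the end of September 2005, "Patient inclusion and pre-data collection will start in 2005", and "The observation period will be 24 months". The ethics section lets patients cancel DMP participation whenever they wish.

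Controls are 4000 AOK patients of non-DMP practices, identified by diabetes tracer medication and age over 50, and matched. Those in another fund's DMP are excluded.

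The analysis is by intention to treat. In Table 1, drop-out from the DMP is an outcome for DMP 1 versus DMP 2 only; the entry for DMP 1 versus control is blank. The primary outcome for the control comparison is the proportion with antidiabetic, antihypertensive and lipid-lowering prescriptions.

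**The concern.** Hypothesis 1 is about the programme: that the DMP is more effective than routine care. The arm that tests it consists of people in the programme on the day of inclusion. Patients who enrolled, found it did not suit them and left before that day are part of what the programme achieved, but they appear nowhere in this comparison. Intention to treat protects only from inclusion onward, and drop-out is not an outcome here.

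Staying in a structured programme is plausibly linked to adherence and motivation, and so to prescriptions, referrals and education. The Background makes a related criticism of the earlier model projects, where "bias because of the preferred inclusion of highly motivated patients can not be excluded". Controls meet no condition of having stayed in a programme, but they do meet a medication condition that the article does not state for DMP 1. A difference between the groups could then reflect who was admitted to each rather than what the DMP does.

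**Working it through.** **1. Time for exits before inclusion.** From 27 February 2003 (Background) to the end of September 2005 (Timeframe) is 31 months, or 2.6 years. From the end of April 2003 (abstract) it is 29 months, or 2.4 years. About 2.5 years is an upper bound. The 2003 dates mark the first accreditation, no start date is given for these practices or states, and patients newly enrolled in 2005 also qualify.

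**2. Selection rules side by side.**

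| Condition | DMP 1 | Control |
|---|---|---|
| AOK insured | yes | yes |
| Practice | in the DMP | outside the DMP |
| Currently in the DMP | required | not applicable |
| Diabetes tracer medication | not stated | required |
| Age over 50 | not stated | required |
| Prior AOK-DMP enrolment | allowed | not excluded |

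Controls are matched; the article does not say on what.

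**3. Shift from missing leavers.** Let r be the outcome proportion in those who stayed, L the share of ever-enrolled patients who left before inclusion, and g the amount by which the leavers' proportion is lower.

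- All ever enrolled: (1 − L)·r + L·(r − g) = r − L·g
- Stayers minus all ever enrolled: L·g

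The article gives neither L nor g, so all values here are assumptions. Results in percentage points:

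| L | g = 5 | g = 10 | g = 20 | g = 30 |
|---|---|---|---|---|
| 0% | 0 | 0 | 0 | 0 |
| 2% | 0.1 | 0.2 | 0.4 | 0.6 |
| 5% | 0.25 | 0.5 | 1.0 | 1.5 |
| 10% | 0.5 | 1.0 | 2.0 | 3.0 |
| 20% | 1.0 | 2.0 | 4.0 | 6.0 |
| 30% | 1.5 | 3.0 | 6.0 | 9.0 |

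Sample size does not enter L·g, so the 4000 controls do not reduce it. If leavers did no worse (g at or below 0), the shift is zero or reversed.

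**4. Shift from the tracer rule.** Suppose the tracer is an antidiabetic drug, which the term implies but the article does not state. Controls are then at or near 100% on the antidiabetic component by construction. If a share u of DMP 1 patients takes no such drug, DMP 1 looks u worse on that component with no true effect. An assumed u of 5% to 30% gives 5 to 30 points. The antihypertensive and lipid-lowering components have no such ceiling. If the matching already covers tracer medication, this shift shrinks or disappears.

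**5. Scale.** The plan's own figure is 200 GPs with 20 patients each at an ICC of 0.05. The article does not give significance level, power, event rates or effect size, so that figure can be neither reproduced nor refuted, and this point does not turn on it. For orientation only: design effect = 1 + 19 × 0.05 = 1.95, and effective size per arm = 100 × 20 / 1.95 = 1026. With an assumed two-sided 5% level, 80% power and a rate near 50%, about 6.2 points are detectable. That applies to DMP 1 versus DMP 2 and is only indicative for the control comparison. On that scale a shift of 2 to 6 points (L of 10% to 30%, g = 20) is about a third to nearly all of the detectable difference.

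**The case against.** The best defence is that the article discloses the weaker status of this comparison. The Discussion calls it quasi-experimental with non-random controls, says "in our case that implementation process has already started" and concedes that "baseline values for patients participating in the DMP have not been documented". DMP 1 is meant to represent the programme as it currently runs, so taking current participants is a choice of question and contradicts nothing in the text. This stands as far as it goes. The Discussion does not name earlier leavers, however, and Hypothesis 1 is not worded for current participants.

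Three stronger readings are tempting, and the defence is right to resist them.

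- **That the controls are unselected.** They are selected on medication, age and practice, and are matched. The selection differs from that of DMP 1; it is not absent.
- **That the bias favours Hypothesis 1.** That would follow for the retention rule alone, if leavers have lower proportions, which the article does not show. The tracer rule can work against DMP 1 on one component of the primary outcome.
- **That failed DMP patients are recycled as routine care.** The exclusion covers only another fund's DMP, so the gap exists. But a former AOK-DMP patient could enter only after changing to a non-DMP practice, or if the practice itself left the DMP.

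The defence also has a point on remedies. An arm of all living, ever-enrolled patients would still condition on survival. The article also draws DMP data from documentation forms, which former participants no longer generate.

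**Conclusion.** The point holds in a limited form. For DMP 1 versus control, DMP 1 is a group of current participants. Patients who left in the up to 2.5 years before inclusion are outside it, nothing in the article brings them back, and controls are chosen by different rules.

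The size cannot be determined from the article. It is zero if nobody left, and 0.1 to 9.0 points for assumed shares of 2% to 30% and assumed gaps of 5 to 30 points. The net direction across both selection rules is also undetermined, so a reader should not conclude that the comparison is tilted towards the DMP.

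The randomised DMP 1 versus DMP 2 comparison is not biased by this. Exits before randomisation affect both arms alike and limit only how far its result generalises.

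**What to change.** For DMP 1 versus control only:

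1. Apply the control selection conditions (tracer medication, age over 50) to DMP 1.
2. Exclude patients with any prior AOK-DMP enrolment from the control group.
3. Word the Hypothesis 1 conclusion for patients who remain in the DMP.
4. If the AOK can supply enrolment history and routine data on former participants, add an analysis of all patients ever enrolled in the DMP 1 practices. State that it still omits those who died, moved practice or changed insurer.

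The cost is a smaller DMP 1 set for this comparison, a narrower conclusion and one extra AOK data query. Step 4 also needs a check that data on former participants are available and may be used, since they lie beyond the DMP forms. If the tracer is an antidiabetic drug, step 1 brings that component near its ceiling in both groups at selection, so it will then carry little information. The randomised comparison needs no change.

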#### Sample size calculation

Sample size calculations for cluster randomized trials differ from sample size calculations for common RCTs requiring a larger number of patients. Based on the main outcome parameters we performed a power calculation with the Cluster Randomization Sample Size Calculator ver.1.02 of the University of Aberdeen on the basis of an ICC of 0,05. Considering possible drop-outs a sample size of 200 GPs will be required (each GP including 20 patients).

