### Patient informed consent

Previous to DMP participation patients already receive written and oral information about the content and extent of the DMP by their treating GPs, i.e. about potential benefits for their health and potential risks. Furthermore, patients are informed that DMP data including medical data will be analyzed. In case of acceptance they have to sign a special DMP participation form.

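### Patients enter after their practice is randomised, with no requirement that DMP participation predates allocation, so enrolment can differ between DMP 1 and DMP 2

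*Protocol article*

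**What the plan says.** Selection of participants in the protocol article gives the order of events. GPs come first: "From those who will accept to participate, 100 GPs will be randomized in the DMP group 1 and 100 in the DMP group 2". The next sentence brings in the patients. All AOK-insured people with type 2 diabetes in these practices qualify if they are in the DMP, and they "participating in the DMP will be included in the study then".

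Timeframe of the study has the same order. "The study team will start to invite GPs at the end of September 2005", and GPs are randomised once they have accepted in writing. On patients it says only "Patient inclusion and pre-data collection will start in 2005", followed by "The observation period will be 24 months". It gives no closing date for inclusion and no link between DMP enrolment and the date of allocation.

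Patient informed consent describes how a patient joins the DMP: "patients already receive written and oral information about the content and extent of the DMP by their treating GPs", after which the patient signs a participation form. The ethics section adds that participation is voluntary and can be ended at any time. Under Intervention, DMP 2 practices receive quality circles, meetings for medical assistants, outreach visits and a website, while DMP 1 practices receive nothing extra.

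**The concern.** In a cluster trial, randomisation balances the clusters. It balances the patients only if the patient list cannot be influenced by the allocation. Here, membership of the list depends on DMP participation. The GP, who is the randomised party, takes part in that step, and the stated order places inclusion after allocation.

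The arm cannot be concealed from practices, because the DMP 2 support is delivered to the GP and the practice team. Its declared purpose is better implementation of the DMP, so a change in who is enrolled is a plausible side effect.

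The primary outcome for DMP 1 against DMP 2 is the proportion of patients at target for HbA1c and blood pressure. A difference between the arms in who enters changes that proportion even if care has no effect. Intention-to-treat analysis does not correct this, because it starts from the patients who were included. The rationale under Aim and design of the study, that cluster randomisation leaves no confounding, is then too strong at patient level.

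**Working it through.** **The plan's own figure.** Sample size calculation states that "a sample size of 200 GPs will be required (each GP including 20 patients" each, with an ICC of 0.05 and an allowance for drop-outs. The article gives no alpha, power, event rates, target difference or drop-out rate, so the 200 GPs can be neither reproduced nor refuted. The point concerns the order of events and does not depend on this figure.

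**Inputs from the article:** 100 GPs per arm, 20 patients per GP, ICC 0.05.

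**Inputs assumed:** 50% at target, two-sided alpha 0.05, no drop-out, no true effect.

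**Step 1: precision.**
- Design effect = 1 + (20 − 1) × 0.05 = 1.95.
- Effective patients per arm = 100 × 20 / 1.95 = 1026.
- Standard error of the difference = √(2 × 0.5 × 0.5 / 1026) = 0.022, or 2.2 points.

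**Step 2: form of the bias.** Let f1 and f2 be the shares of each arm's patients who enrol after allocation. Let g1 and g2 be the amounts by which their target attainment differs from that of the other patients in their arm. The net bias is f2·g2 − f1·g1. If both arms enrol 15% with the same case mix, it is zero. With a common difference g it reduces to (f2 − f1)·g:
- 10 percentage points of excess share × a 10-point difference = 1 point;
- 20 × 10, or 10 × 20 = 2 points;
- 20 × 20 = 4 points.

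None of these shares or differences is in the article. The sign of g is also unknown.

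**Step 3: effect on the test.** For a net bias b, the rejection probability under no true effect is [1 − Φ(1.96 − b/SE)] + Φ(−1.96 − b/SE).

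| Net bias | b/SE | Type I error at 50% | Type I error at 30% |
|---|---|---|---|
| 0 | 0 | 5% | 5% |
| 1 point | 0.45 | 7.4% | 7.8% |
| 2 points | 0.91 | 14.8% | 16.7% |
| 4 points | 1.81 | 44.1% | 50.7% |

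The b/SE column is for 50%. A bias of the opposite sign gives the same two-sided values. Loss of practices would widen the standard error and lower these figures: with 20% lost, the effective number is 80 × 20 / 1.95 = 821 per arm.

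**Step 4: scale.** Under the same assumptions, the design detects about 6.2 points from 50% with 80% power. A net bias of 1 to 4 points is not negligible against a difference of that order.

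**The case against.** The strongest reply is that the article describes a population largely in place already. The first type 2 diabetes DMP was accredited in 2003, and only GPs already in the programme are invited. The Discussion says implementation is under way. All eligible patients are taken, and all data come from the AOK, so no practice hand-picks trial patients. The DMP 2 meetings take place twice a year and the visits once a year, so they may have had little time to alter enrolment before inclusion. None of the components mentions enrolling more patients. Finally, the date of an insurer's data extract is a detail that a condensed article may leave to the full protocol.

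Much of this stands. It rules out free selection by the GP and probably limits the size of the bias. It does not fix the list before allocation. The article does more than omit a date: it states an order, with inclusion after randomisation and current DMP participation as the criterion.

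Three stronger readings are tempting, and the article supports none of them:
- A reader might infer that GPs draw up the patient list, perhaps from the phrase about each GP including 20 patients. Selection of participants takes all eligible patients instead, and no recruitment by the GP is described.
- A reader might assume that newly enrolled patients are milder and so favour DMP 2. Nothing in the article says so; they could equally be less well controlled.
- A reader might treat every DMP 2 patient enrolled after allocation as a source of bias. DMP 1 practices can enrol too, and only the difference between the arms counts.

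**Conclusion.** The point holds as a weakness in the stated inclusion rule. Followed as written, it lets patient entry differ between DMP 1 and DMP 2 after an allocation that practices know about, and so lets the primary comparison be biased in either direction. That practices know their arm is an inference from the open nature of the DMP 2 support, but a safe one.

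The article does not show that differential enrolment will occur, and its size cannot be estimated from the article. It may be small if most patients joined before 2005. The error rates of about 7%, 15% and 44% illustrate net biases of 1, 2 and 4 points under the stated assumptions. They are not predictions, and the last needs both assumed inputs at their upper values. The remedy is cheap, so the rule should be changed even though the bias may prove minor.

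**What to change.** Define the primary-analysis cohort, identically in both arms, as all AOK-insured patients with type 2 diabetes recorded in AOK data as DMP participants of a consenting practice on a fixed date before that practice's randomisation. Analyse patients enrolled after that date separately. This sets both shares of later enrolees in the primary analysis to zero, so the enrolment bias is zero. At 20 patients per practice, the design effect stays at 1.95.

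Patients who leave the DMP after that date should stay in the intention-to-treat denominator. In the DMP arms, data come from the DMP documentation forms, so leavers will have no later HbA1c or blood pressure values from that source. Their missing values fall under the rule already stated in Data collection and analysis (last observation carried forward).

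The cost is one sentence in the protocol and one dated AOK list per practice. The downside is that later enrolees do not count in the primary analysis.

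Selection of participants also excludes incomplete participation in the interventions, in DMP 2 only. That is a separate arm-specific selection after randomisation. This change does not solve it, and it needs its own correction.

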### Data collection and analysis

All data will be provided by the AOK. Data of the DMP groups are retrieved by the DMP documentation forms which have to be completed routinely every 3 to 6 months during the scheduled DMP visits of participating patients. The information about the tracer medication identifying patients of the control group is also provided by the AOK. The data reporting will follow the CONSORT recommendations for cluster randomized trials [16].

Data analysis will be performed according to the intention-to-treat (ITT) method. For missing data the 'last observation carried forward' -method will be used.

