### Intervention

The minimum requirements for the Diabetes-DMP are regulated by law and defined in the RSAV [10]. According to the legal regulations the intervention in the DMP1 group comprises consultations at 3- or 6-months intervals. During these consultations a detailed diabetes-specific anamnesis and physical examination incl. taking blood pressure and an analysis of HbA1c are carried out. Furthermore agreements are made concerning further treatment, e.g. target values for HbA1c and blood pressure and participation on patient education programs for diabetes or hypertension. All medical findings as well as the current medication have to be documented within structured, standardized documentation sheets at each consultation. If required a referral to a specialist (e.g. ophthalmologist) will be arranged. Furthermore the GPs get a special diabetes-handbook including current, evidence-based information about diabetes therapy. The GPs participating in the DMP1 group will receive no additional intervention.

There are major difficulties introducing new evidence into general practice requiring comprehensive implementation support at different levels (patients, doctors, practice team) [17,18]. Therefore, in the DMP 2 group implementation support at the level of doctors and practice team will be provided. In addition to the clinical interventions at patients level in the DMP group 1 several components aiming at optimizing the implementation process are provided in this group (= implementation interventions) (Table 2).

**Table 2 T2:** Implementation Interventions in DMP 2 group

**Interventions**	**Description**
Interactive quality circle meetings	During these meetings all aspects of evidence based treatment of diabetes in a primary care setting will be discussed (2 × per year).
Educational meetings for medical assistants	During these meetings medical assistants will be supported in finding individual strategies for optimal implementation of the DMP in their practices (2 × per year).
Outreach visits	During these meetings individual problems within the implementation process of the DMP will be discussed with the GP and the assistant team (1 × per year)
Homepage with "best practice" examples	Detailed information for the praxis team about Diabetes-DMP incl. case studies via internet (electronic individual feedback)

The control group represents routine care without DMP. There will be no intervention at all.

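### The exclusion for incomplete participation applies after randomisation and in DMP 2 only, which conflicts with the stated intention-to-treat analysis and could bias the randomised comparison

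*Protocol article*

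**What the plan says.** Four statements in the protocol article bear on this point.

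- **Allocation** (Selection of participants): "100 GPs will be randomized in the DMP group 1 and 100 in the DMP group 2". Patients with type 2 diabetes in these practices who are insured with the AOK and enrolled in the DMP are then included.
- **Exclusion** (same section): "Incomplete participation in the interventions will be an exclusion criterion in the DMP group 2". The sentence names no unit (practice or patient) and does not define incomplete. No counterpart is given for DMP 1.
- **Analysis** (Data collection and analysis): "Data analysis will be performed according to the intention-to-treat (ITT) method". No exception is stated. The next sentence reads "For missing data the 'last observation carried forward' -method will be used".
- **Interventions** (Intervention, with Table 2): "in the DMP 2 group implementation support at the level of doctors and practice team will be provided", whereas "The GPs participating in the DMP1 group will receive no additional intervention". Table 2 schedules quality circles twice a year, meetings for medical assistants twice a year and an outreach visit once a year. Under Timeframe of the study: "The observation period will be 24 months".

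The article nowhere says that excluded units stay in the intention-to-treat set, or that the exclusion serves only a per-protocol analysis.

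**The concern.** Intention-to-treat keeps every randomised unit in its allocated arm, whatever it goes on to do. A rule that removes units for what they did after allocation, in one arm only, does the opposite. If it reaches the primary analysis, DMP 2 is represented by its fully participating practices and DMP 1 by all of its practices.

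The contrast affected is the only randomised one in the study, and its primary outcome is attainment of the HbA1c and blood pressure targets. The section on aim and design justifies cluster randomisation by internal validity and freedom from confounding, which such a rule would give up. The Background also names selection of motivated patients as a possible bias in the earlier model projects. Selecting the keener practices in one arm would be a related problem.

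**Working it through.** **1. Is the rule post-randomisation?** It applies only to DMP 2, and membership of that group is created by randomisation. Table 2 gives 2 + 2 + 1 = 5 scheduled contacts a year, or 10 over 24 months. Completeness cannot be known at baseline.

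**2. Is it one-sided?** Yes. DMP 1 receives none of these interventions, so no DMP 1 practice can fail the criterion.

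**3. Which unit?** This is inferred. The added interventions all act on the doctor and practice team, so the practice is the natural unit.

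**4. Does the missing-data rule repair it?** No. Last observation carried forward fills gaps for units in the analysis; it does not bring excluded units back.

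**5. Precision of the design.** The 200 practices cannot be recalculated from the article's inputs, and the point does not depend on them. With 20 patients per practice and ICC 0.05, the design effect is 1 + 19 × 0.05 = 1.95, so 2000 / 1.95 ≈ 1026 effective patients per arm. At an assumed two-sided alpha of 0.05 and DMP 1 rates of 30–50%, the detectable difference is about 5.8–6.2 points at 80% power.

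**6. Bias under no true effect.** Assumed: target rate 50%; a share e of DMP 2 practices, those participating least, is dropped; correlation r between a practice's participation and its target rate.

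- Between-practice SD = √(0.05 × 0.5 × 0.5) = 0.1118.
- Bias = r × 0.1118 × φ(z_e) / (1 − e), where z_e is the normal quantile of e and φ the normal density.
- Example, e = 30%, r = 0.5: 0.5 × 0.1118 × 0.3477 / 0.70 = 0.0278.

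A simulation (10,000 trials, 100 practices per arm, 20 patients each, t-test on practice means) gave the type I error and confirmed the formula to within 0.1 point:

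| Excluded | r = 0: error | r = 0.3: bias, formula (simulated), points | r = 0.3: error | r = 0.5: bias, formula (simulated), points | r = 0.5: error |
|---|---|---|---|---|---|
| 10% | 4.9% | 0.65 (0.63) | 6.3% | 1.09 (1.10) | 8.5% |
| 20% | 5.1% | 1.17 (1.18) | 8.4% | 1.96 (1.97) | 13.7% |
| 30% | 5.0% | 1.67 (1.65) | 10.6% | 2.78 (2.71) | 20.0% |
| 40% | 4.9% | 2.16 (2.12) | 13.5% | 3.60 (3.57) | 29.8% |

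Where r > 0, nearly all of the excess rejections favour DMP 2.

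**7. Precision alone (r = 0).** The standard error grows by √[(1/k + 1/100) / (2/100)], with k practices left in DMP 2: about 3% for k = 90 and 10% for k = 70.

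**8. A more severe case.** Assume 40% excluded and target attainment of 45% in complete and 35% in incomplete practices.

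- DMP 1 overall: 0.6 × 0.45 + 0.4 × 0.35 = 0.41, so the bias is 0.04.
- Effective sizes: 60 × 20 / 1.95 ≈ 615 and 1026.
- SE = √(0.45 × 0.55 / 615 + 0.41 × 0.59 / 1026) = 0.0253; z = 0.04 / 0.0253 = 1.58; rejection probability about 35%.
- With 45% against 40% instead, the bias is 2 points and the rejection probability about 12%.

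**The case against.** The strongest reply is that the exclusion sentence stands in a section on selection, while the only sentence about analysis says intention-to-treat. A condensed article may name a removal criterion and leave the analysis sets to the full protocol or analysis plan, so that intention-to-treat governs and the criterion only marks a per-protocol population. The second hypothesis also concerns an optimally implemented programme, which gives the rule a purpose.

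Part of this stands. The article does not rule that reading out, so one cannot assert that practices will be dropped from the primary analysis. But it does not state that reading either. It gives two rules that conflict as written, which is more than omitted detail. An interest in full implementation explains the rule without making one-arm exclusion a valid way to estimate that effect.

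It is also fair to object that the direction is not given. At r = 0 the error stays near 5%, and the Background remark is about patients in uncontrolled projects, not about practices in this trial. On precision, the sample size section says that drop-outs were considered, so some loss of practices may already be covered.

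**Conclusion.** The concern holds as a conflict between two current statements. A one-arm criterion that can be assessed only after randomisation is incompatible with an unqualified intention-to-treat analysis, and applying it to the primary analysis would break the randomised comparison. Under the moderate assumptions (10–30% excluded, r = 0.3–0.5), the spurious gain for DMP 2 is about 0.6 to 2.8 points, against a detectable difference of about 6 points, and the type I error is about 6–20%. The exclusion share, the correlation, the 50% target rate and the practice as unit are all assumptions.

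A reader might infer two stronger claims that the article does not support.

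- **That the plan necessarily favours DMP 2.** This needs better-participating practices also to reach targets more often, which is plausible but not stated.
- **That 40 to 65 of the 100 DMP 2 practices would be lost and the error would be 35%.** The losses follow from 0.95^10 = 0.60 or 0.90^10 = 0.35 complete practices. That requires complete to mean 10 of 10 contacts, which the article does not say, and independent attendance; positive correlation within practices would leave more of them complete. The 35% further needs the 10-point gap. It marks a severe case, not the expected one.

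**What to change.** - Remove the participation criterion from the primary analysis. State that all 200 randomised practices and their eligible patients are analysed in the allocated arm, whatever their participation.
- Report participation in the DMP 2 interventions as a process measure.
- If the question of full implementation matters, keep the criterion for a labelled secondary per-protocol or sensitivity analysis. Define incomplete participation and the unit it applies to in advance.
- If a complier-average analysis is added with full participation as the treatment, state the assumption it needs: that partial participation has no effect. This is doubtful here, since a practice attending most meetings may well benefit. A graded measure of participation is the alternative.

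The cost is small: one sentence reworded, one definition and one secondary analysis described. Outcomes come from routine DMP documentation supplied by the AOK, so data from incompletely participating practices should remain available. The downside is that the intention-to-treat effect may be smaller than the effect under full participation.
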